## Abstract

**Background:**

There are no prospective trials comparing the two main reconstructive options after colectomy for Ulcerative colitis, ileal pouch anal anastomosis and ileorectal anastomosis. An attempt on a randomized controlled trial has been made but after receiving standardized information patients insisted on choosing operation themselves.

**Methods:**

Adult Ulcerative colitis patients subjected to colectomy eligible for both ileal pouch anastomosis and ileorectal anastomosis are asked to participate and after receiving standardized information the get to choose reconstructive method. Patients declining reconstruction or not considered eligible for both methods will be followed as controls. The CRUISE study is a prospective, non-randomized, multi-center, open-label, controlled trial on satisfaction, QoL, function, and complications between ileal pouch anal anastomosis and ileorectal anastomosis.

**Discussion:**

Reconstruction after colectomy is a morbidity-associated as well as a resource-intensive activity with the sole purpose of enhancing function, QoL and patient satisfaction. The aim of this study is to provide the best possible information on the risks and benefits of each reconstructive treatment.

**Trial registration:**

ClinicalTrials.gov Identifier: NCT05628701

## Introduction

Ulcerative Colitis (UC) is a chronic inflammatory bowel disease (IBD) restricted to the mucosa of the rectum and colon [1, 2]. The corner stone of UC treatment is pharmacological [3]. For about 10–15% of patients with UC medical treatment is not sufficient to induce/maintain remission or dysplasia/cancer occurs, and a colectomy will eventually be required [4, 5]. Although there are instances where a proctocolectomy with concomitant reconstruction is performed the recommended strategy for UC is usually a subtotal colectomy and reconstruction at a later stage [6, 7]. In a subtotal colectomy the distal colon is divided just above the promontory of the sacrum leaving a rectal remnant. The colon is removed and the terminal ileum is brought out through the abdominal wall as a stoma.

After subtotal colectomy there are four available options for patients. A reasonable option is to not proceed for further surgery and leave the rectum in place—the patient will live with a permanent ileostomy. Another option is the ileal pouch anal anastomosis (IPAA) where the rectum is removed and a pouch is created from the distal part of the ileum which is stapled or sutured to the anal canal or just above [8]. The IPAA is considered the gold standard reconstruction after subtotal colectomy [9]. A third option is the ileorectal anastomosis (IRA) where the rectum is left in place and the terminal ileum is stapled or handsewn to the top of the rectal remnant [10]. Then, for the rare instances that the patient is not suitable for either IPAA or IRA but still wants to avoid a stoma appliance, the Kock pouch is an option. The Kock pouch is a continent ileostomy that is actively emptied with a tube through the abdominal wall [11]. However, the Kock pouch is not commonly performed compared to the above options and will not be evaluated in this study. In a nationwide register study comparing Sweden and England only 46% and 33% of patients treated with colectomy received any reconstruction, respectively [12]. Whether the patients were offered reconstruction is unknown.

There are no randomized controlled trials (RCT) comparing IRA to IPAA. In a decision model using a Markov simulation in comparing IRA with IPAA in UC, the former was the preferred treatment option when quality-adjusted life-years were the outcome, while higher life-years was true for the latter [13]. An attempt of an RCT was conducted in Sweden led by Linköping starting late 2000 but after receiving adequate and standardized preoperative information the patients insisted on choosing surgical method, with a similar spread between the two options, and refused to be randomized. Therefore, the study was stopped. No protocol or results where, unfortunately, ever published from that RCT.

## Method/design

### Study objectives

To compare, in a prospective setting, patient satisfaction, QoL, function, and complications between IRA and IPAA and permanent stoma among patients with UC subjected to subtotal colectomy.

This study aims to answer what type of reconstruction, if any, UC-patients asks for following a colectomy, their satisfaction with the treatment, postoperative function and QoL. The results may have a large impact on future treatment recommendations.

### Study design

The CRUISE study is a prospective, non-randomized, non-blinded, multi-center, controlled trial on satisfaction, QoL, function, and complications between IRA and IPAA and permanent stoma among adult UC patients subjected to subtotal colectomy. All adult UC patients scheduled for a subtotal colectomy will be asked for informed consent. The patients will then be presented standardized written and video recorded information on the available reconstructive options. If the patient meets the inclusion criteria, their preferred choice of IRA or IPAA will assign them to one of the study arms. Patients that do not meet the inclusion criteria or fulfill any of the exclusion criteria (e.g. not suitable for an IRA) or refrain reconstruction will be asked to participate as controls.

### Endpoints

The primary endpoint is satisfaction with the choice of reconstructive method or permanent stoma. Secondary endpoints are QoL, sexual function, bowel function and complications.

### Study population

The study population consists of all adult UC patients subjected to subtotal colectomy and eligible for both IRA and IPAA presenting at any of the participating centers.

Inclusion criteria are patients with UC aged between 18 and 60, scheduled for or have previously undergone subtotal colectomy and ileostomy. Patients should have sufficient rectal compliance and controllable inflammation in the rectal using topical 5-ASA only (Fig. 1).

**Fig. 1 Fig1:**
[figure not shown]
Inclusion and Exclusion criteria

Exclusion criteria are rectal inflammation of Mayo Score > 1 [14], poor sphincter function, perianal disease, uncertainty regarding UC diagnosis (IBD-U or possible Crohn’s disease), previous colorectal cancer or severe dysplasia (reported to the cancer registry), PSC diagnosis or > 2 year since subtotal colectomy (Fig. 1).

### Sample size

The only available study on patient satisfaction, our primary outcome, between IRA and IPAA reports 98% and 88% satisfaction for the methods respectively [15]. However, they only asked the IRA patients that still had their IRA in place after a mean of 11 years making it a little difficult to interpret. Another study compared QALYs between IRA and IPAA and reports a mean of 33.42 for IRA and a mean of 31.57 for IPAA [13]. With an estimated 3 SD (it was 2.8 for IRA and 4.5 for IPAA) and the significance level 0.05 and 80% power that difference would require 43 patients in each group to demonstrate a difference. Due to the mentioned shortcomings of the study comparing satisfaction we regard the latter study more relevant and decided to aim at a minimum of 50 patients in each group. Deliberately a little over the power estimation to avoid any effect of possible loss to follow-up.

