### Statistical analysis

Analysis will be conducted according to the intention-to-treat principal. The primary outcome satisfaction, a proportion, will be compared with chi-square test. For the primary outcome two-tailed tests will be applied since the null hypothesis is that there is no difference between the two reconstructive methods. Secondary outcomes assumed to be normally distributed will be compared between the two study arms using t-tests. Functional and QoL variables will be analyzed with mixed model ANOVA analysis. Time to failure will be analyzed with multivariate cox-regression analysis. Kaplan–Meier curves will be constructed and compared with log-rank tests. Repeating events, such as reoperations, will be analyzed with multivariate Poisson-regression.

There is no data and safety monitoring committee since all treatment is according to established practice. We do not plan to perform any interim analysis.

From a statistical point of view our choice of primary endpoint is not optimal because we have no reason to expect any difference between the two study arms. Still, to our opinion, this is the most important outcome measure.

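### The sample size uses an unexplained SD of 3 against quoted source SDs of 2.8 and 4.5; on those SDs the QALY comparison needs about 66 per group, and 50 gives about 68% power with no margin for loss

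*Protocol article*

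**What the plan says.** The Sample size section first sets aside a study of satisfaction (98% for IRA, 88% for IPAA), because only patients whose IRA was still in place were asked. It then turns to a study of QALYs, which "reports a mean of 33.42 for IRA and a mean of 31.57 for IPAA". The spread is given as "With an estimated 3 SD (it was 2.8 for IRA and 4.5 for IPAA"). With "the significance level 0.05 and 80% power", the section concludes "that difference would require 43 patients in each group to demonstrate a difference".

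The target is then set at no fewer than 50 per group, with this explanation: "Deliberately a little over the power estimation to avoid any effect of possible loss to follow-up". No expected loss rate is stated.

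Three other places bear on the point. The Introduction describes the QALY source as a decision model based on Markov simulation. The Endpoints section makes satisfaction the primary endpoint and does not list QALYs. The Statistical analysis section compares satisfaction by chi-square test and says "For the primary outcome two-tailed tests will be applied".

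**The concern.** The number needed to compare two means depends on the variances of both groups. The section reports both source SDs and then calculates with a value close to the smaller one. It is below the simple average of the two (3.65) and below their root mean square (3.75), and no reason is given. The choice is favourable: it lowers the required number by about a third.

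This is the only power calculation in the article. A reader takes from it that the study has at least 80% power for the stated difference and a reserve against loss. If the SDs quoted from the source are the right ones, neither statement is true.

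**Working it through.** **Inputs** (Sample size section, except sidedness)
- QALY means 33.42 (IRA) and 31.57 (IPAA), so the difference is d = 33.42 − 31.57 = 1.85.
- SD used: 3. Source SDs: 2.8 (IRA) and 4.5 (IPAA).
- Alpha 0.05 and power 80%. The section does not state sidedness. Two-sided is stated for the primary outcome in the Statistical analysis section, and only two-sided reproduces 43 (one-sided gives 33).
- Target 50 per group, equal groups.

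**Step 1. Reproduce the plan's figure.** The normal approximation is n = 2 × SD² × (1.960 + 0.842)² / d², with (1.960 + 0.842)² = 7.849.
- SD 3: n = 2 × 9 × 7.849 / 3.4225 = 41.3, so 42.
- Two-sample t-test (noncentral t): 42 per group gives 79.7% and 43 gives 80.7%, so 43.

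The stated 43 is reproduced exactly. With SD 3, 50 per group gives 86% power.

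**Step 2. Combine the quoted SDs.** With n per group, the variance of the difference in means is (2.8² + 4.5²)/n. The equivalent common SD is √((2.8² + 4.5²)/2) = √((7.84 + 20.25)/2) = √14.045 = 3.75.

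**Step 3. Recompute by the same method.**
- Normal approximation: n = 2 × 14.045 × 7.849 / 3.4225 = 64.4, so 65.
- t-test: 65 per group gives 79.8% (79.6% with Welch degrees of freedom) and 66 gives 80.4% (80.3%), so 66.
- Power at 50 per group: 68.6% (Welch 68.4%; normal approximation 69.4%).
- Power at 50 − 7 = 43 per group: 61.9% (Welch 61.7%; normal approximation 62.9%).

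**Step 4. Does the result depend on how the SDs are combined?** (t-test)

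| Common SD | Basis | n per group for 80% | Power at 50 |
|---|---|---|---|
| 2.8 | IRA value in both groups | 37 | 91% |
| 3 | plan | 43 | 86% |
| 3.65 | simple average | 63 | 71% |
| 3.75 | root mean square | 66 | 69% (Welch 68%) |
| 4.5 | IPAA value in both groups | 94 | 53% |

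Fifty per group reaches 80% power only if the common SD is about 3.27 or less. Neither average of the quoted SDs is that small.

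**Step 5. The primary test, for orientation.** For satisfaction of 98% versus 88%, two-sided 0.05, the usual two-proportion formula gives about 102 per group for 80% power (121 with continuity correction). Power at 50 per group is about 50%.

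**The case against.** The strongest reply is that nothing has been miscalculated or hidden. SD 3 is a printed input, it is called an estimate, the source SDs stand beside it, and 43 follows from it. That is correct. A reader might infer an arithmetic error, but the document does not support that reading. The fault is an unexplained assumption that departs from the source in the favourable direction.

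Second, 2.8 and 4.5 are outputs of a simulation model, not observations on patients like those in this trial, who are aged 18 to 60 with little rectal inflammation and are followed for 5 years. This also stands. It means that 66 and 68% are what the cited source implies, not the true requirement. It gives no support to 3 either, and the plan takes its difference of 1.85 from the same model.

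Third, QALYs are not an endpoint, so a reader who took 68% as the power of this trial would go too far. It applies to a comparison that the article does not plan. The mismatch between the calculation and the primary endpoint is a separate and larger weakness, and correcting the SD does not cure it.

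Fourth, a reader might infer that the gap between 43 and 50 (7 of 50, or 14%) is too small for a 5-year schedule. The document gives no expected loss rate, so it cannot show this. On the plan's own SD the margin exists. It disappears only when the source SDs are used.

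**Conclusion.** The point holds as an unjustified planning assumption with a sizeable effect. On the SDs that the section itself quotes, the requirement rises from 43 to about 66 per group. The target of 50 is then 16 per group short before anyone is lost. Power for the QALY difference is about 68% at 50 per group and about 62% if 7 per group are lost, so the reserve against loss is not there.

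This rests on a difference of 1.85, two-sided 0.05, equal groups and the source SDs taken at face value. The finding that 50 falls short does not depend on t-test versus normal approximation, or on which of the two averages is used. It would change only if a common SD of about 3.27 or less could be justified. It says nothing about power for satisfaction.

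**What to change.** In the Sample size section:

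1. Restate the QALY calculation with the quoted SDs (about 66 per group for 80% power; about 68% at 50 per group, about 62% at 43), or give the reason for SD 3.
2. Delete the statement that 50 exceeds the requirement and removes any effect of loss. If a loss allowance is wanted, state the assumed rate.
3. Say that this power concerns a QALY difference taken from a simulation model and not the primary endpoint.
4. Preferably, replace the calculation with the power of the primary chi-square test at 50 per group, about 50% for 98% versus 88%, keeping the reservation already expressed about that source.

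The cost is a sentence or two and a less favourable power figure. No endpoint, analysis or trial procedure changes.

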#### Time frame

Baseline data will be collected after colectomy for all patients. The reconstructed patients will then be followed at 2 months, 6 months, 1 year, 2 years and 5 years. Those patients that receive a loop ileostomy at reconstruction will also be followed 2 months after reconstruction before closure of the loop. For those patients the loop closure is considered the index operation. The patients that choose to (or are deemed to) keep their end ileostomies will be followed at 6 months, 1 year, 2 years and 5 years after colectomy (Fig. 3). The recruiting of patients started in March 2017.

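### The 80% power and 43 (then 50) patients per arm are for modelled QALYs; for the actual primary test, satisfaction by chi-square, 50 per arm gives about 51% power on the only rates cited

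*Protocol article*

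**What the plan says.** The Endpoints section fixes the primary outcome: "The primary endpoint is satisfaction with the choice of reconstructive method or permanent stoma". The Statistical analysis section fixes its scale and test: "The primary outcome satisfaction, a proportion, will be compared with chi-square test". It also makes the test two-sided: "For the primary outcome two-tailed tests will be applied since the null hypothesis is that there is no difference between the two reconstructive methods".

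The Sample size section starts from that outcome. It cites one study that "reports 98% and 88% satisfaction for the methods respectively" (IRA and IPAA), then sets it aside because only IRA patients whose anastomosis was still in place after a mean of 11 years had been asked. It turns to a study of QALYs with means of 33.42 (IRA) and 31.57 (IPAA), assumes an SD of 3 (source SDs 2.8 and 4.5), and concludes that at the 0.05 level and with "80% power that difference would require 43 patients in each group to demonstrate a difference". The target is then set at a minimum of 50 per group to cover loss to follow-up.

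The Introduction cites the same QALY reference as "In a decision model using a Markov simulation in comparing IRA with IPAA in UC". On follow-up, the Time frame section says: "The reconstructed patients will then be followed at 2 months, 6 months, 1 year, 2 years and 5 years".

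No power or precision is given for satisfaction.

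**The concern.** A sample size statement should tell the reader what the primary comparison can detect. This one describes a comparison of two means on a variable that appears among neither the primary nor the secondary endpoints and has no analysis in the Statistical analysis section. The SF-36 is collected, but no utility or QALY derivation is stated.

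The borrowed effect also does not fit the trial. A patient followed for 5 years can accrue at most about 5 QALYs, so means of 31 to 33 are out of reach. A gap of 1.85 within 5 years would need an average utility difference of 1.85 / 5 = 0.37 throughout. In the source, 1.85 is only 1.85 / 33.42 = 5.5% of the IRA mean.

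What is at stake is how a null result is read. The authors expect no difference in satisfaction, so a non-significant chi-square test is the likely outcome. A reader who believes the trial had 80% power will take that as good evidence that the two operations satisfy patients equally.

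**Working it through.** **Inputs**

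- Sample size section: QALY means 33.42 and 31.57, SD 3 (source SDs 2.8 and 4.5), alpha 0.05, power 80%, 43 then at least 50 per group, cited satisfaction 98% v 88%.
- Statistical analysis section: chi-square test, two-sided.

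**Step 1. Reproduce the plan's figure.** The difference is 33.42 − 31.57 = 1.85. The normal approximation is n = 2(1.960 + 0.842)² × 3² / 1.85² = 41.3, so 42 per group. The t-test version gives 42.3, so 43. The stated figure reproduces.

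A side point: the root mean square of the two source SDs is √[(2.8² + 4.5²)/2] = 3.75. With that SD even the QALY comparison would need about 65 or 66 per group, and 50 would give about 69% power.

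**Step 2. Power of the planned primary test at 98% v 88%.** The pooled rate is 0.93.

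- Pooled normal approximation at 50 per arm: z = [0.10 − 1.960√(2 × 0.93 × 0.07 / 50)] / √[(0.98 × 0.02 + 0.88 × 0.12) / 50], which is approximately 0, so power is 50.0%.
- Exact power sums the binomial probabilities of every 2×2 table that the test rejects:

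| Per arm | Pearson chi-square | With continuity correction | Fisher |
|---|---|---|---|
| 50 | 51.2% | 31.3% | 31.3% |
| 43 | 50.0% | 22.9% | 23.5% |

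**Step 3. Size needed for 80% power at those rates.** The pooled-variance formula is n = [1.960√(2 × 0.93 × 0.07) + 0.842√(0.98 × 0.02 + 0.88 × 0.12)]² / 0.10² = (0.7072 + 0.2978)² / 0.01 = 101.0. Unrounded this is 101.005, so strictly 102 per arm; with a continuity correction the formula gives 121. By exact enumeration, Pearson power first reaches 80% at 93 per arm.

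**Step 4. Lower IRA satisfaction.** If the 98% is too high and IPAA stays at 88%, exact power at 50 per arm is:

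| IRA rate | Pearson | With continuity correction |
|---|---|---|
| 95% | 23% | 12% |
| 93% | 13% | 6% |
| 90% | 6% | 3% |

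**Step 5. What 50 per arm can do.** The smallest gap with 80% exact power:

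| Rate in the better arm | Pearson | With continuity correction |
|---|---|---|
| 98% | about 15.5 points | about 19 points |
| 90% | about 22.5 points | about 24.5 points |

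The 95% confidence half-width for the difference, 1.96√[2p(1 − p)/50], is 11.8 points at p = 0.90 and 10.0 points at p = 0.93.

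**The case against.** The strongest reply is that the authors chose openly and for a reason. They explain why the satisfaction study is hard to interpret, they tie the 80% to the QALY difference and never claim it for satisfaction, and the Statistical analysis section concedes that the primary endpoint is statistically not ideal because no difference is expected. On this view 98% v 88% is not the trial's design assumption, so 51% is not the trial's power. There is also no arithmetic error in the 43.

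Part of this stands. The sum is correct; the fault is that it is done on the wrong variable. The 51% is power under one cited scenario and is not a ceiling, since a larger true gap would give more. That the QALYs are lifetime totals is an inference from the size of the means and the type of model; the article does not say so, and the point does not depend on it.

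The rest does not rescue the claim. Asking only patients whose IRA survived probably inflates the 98%, which makes the true gap more likely smaller than 10 points and power lower. Doubt about a rate is a reason to show a range of rates, not to change the variable. The concession about the endpoint gives no power or precision for the primary test, and it sits badly with a calculation built to detect a difference. Nor is this a matter left to a fuller document: the article publishes a power figure, and that figure does not apply to its primary test.

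**Conclusion.** The concern holds and must be fixed. The stated 80% power and the 43 per group, raised to 50, rest on a variable the trial does not analyse and on totals it cannot observe.

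For the two-sided chi-square test on satisfaction, 50 per arm gives about 51% power uncorrected, or 31% with a continuity correction, at 98% v 88%. Power is lower still if the true gap is smaller or patients are lost. Power of 80% would need a difference of roughly 15 to 23 points uncorrected, or 19 to 25 points corrected.

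These figures assume 50 evaluable patients in each arm, independent binary responses, alpha 0.05 two-sided, and a higher satisfaction rate between 90% and 98%.

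**What to change.** Rewrite the Sample size paragraph. Remove the QALY calculation and the 80% claim, keep the authors' caveat about the satisfaction source, and state what the available number can do. For example:

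> The target of 50 patients per arm was not derived from a power calculation for satisfaction. If satisfaction were 98% and 88%, the two-sided chi-square test would have about 51% power (31% with continuity correction). The 98% comes only from patients whose IRA was still in place; if the true rate were 95% or 93% against 88%, power would be about 23% or 13% (12% or 6% with continuity correction). Power reaches 80% only for differences of about 15 to 23 points (19 to 25 with continuity correction). The 95% confidence interval for the difference has a half-width of about 10 to 12 points when satisfaction is 93% to 90%.

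State whether the chi-square test uses a continuity correction and keep only the matching figures. Present the primary result as a difference in proportions with its 95% confidence interval, so that a non-significant test is not read as evidence of equality.

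The cost is one rewritten paragraph and a less favourable power statement. Sample size, endpoint, test and conduct stay as they are.
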